#### Giving outcomes a value

In the final part of this process, we give the identified outcomes a monetary value using financial proxies that reflect that importance of the outcome to stakeholders (see Table 3). In consultation with the YAC, a sense of connectedness and sense of belonging was considered similar to having friends. Powedthavee (64) identified the economic value of making and having new friends, in addition to existing friends, and this value was subsequently updated and converted to Australian dollars (See Table 3). Given that the original value was calculated in 2007, we adjusted it for inflation to reflect its current purchasing power, ensuring consistency with contemporary economic conditions. Although using a currency converter may not be the ideal method, this approach, when combined with inflation adjustments, provides a reasonable approximation of the value in today’s terms.

**Table 3 tab3:** SROI stage 3 outcomes.

Stakeholder		Stage 3				
Satellite young person participants		The outcomes (what changes)				
	Outcome	How will we know if the outcome has occurred	Source	How can you value the change?	Value $AUD for six-month period	Source
		Measured how?	Where this information comes from	What proxy is used to value the change?	Value of the change	Where this information comes from
	Sense of belonging and increased connectedness	Feel more connected to other young people living in similar circumstances	SDQ: Prosocial behaviour subscale (child and parent versions) LSAC items on connectedness Interviews with children/youth	Powdthavee (64) identified the economic value of friends (in addition to existing friends): 15,500 pounds per year in 2007 is equivalent to 23,903.38 pounds in 2022, converted to 2022 AUD 42,818.76 *per annum*	$21,861.38	Powdthavee (64).
		Reduced feelings of isolation and increased feelings of belonging				
	Increased resilience	Decreased mental health crises	CYRM-R total score KCS, completed by children aged 10 years and under; CASQ, completed by older children, adolescents and young adults Interviews with children/youth	The Australian Psychological Society (APS) recommends $300 per hour per child/young person for psychological services – 14 sessions	$4,200 per child/young person	APS website: https://psychology.org.au/psychology/about-psychology/what-it-costs
	Sense of hope, optimism and possibility	Increased hope for the future that results in planning for future activities/goals, agency	Children’s Hope Scale Interviews with children/youth	Cost of a mentor such as what might be available from the Big Brothers, Big Sisters mentoring program: $2,500 per person for 12 months	$1,250	Big Brother, Big Sisters of Australia Annual Report 2019–2020 BBBS_Annual_Report_2019-2020.pdf (bigbrothersbigsisters.org.au)

We also identified a financial proxy for resilience. For the young people involved in these programs, resilience refers to achieving positive outcomes (inclusive of wellbeing) despite coming from challenging backgrounds, and adaptively coping with current stressors (see Figure 1, Theory of Change). According to Olsson et al. (48), promoting resilience at an individual level involves developing personal coping skills and resources, both of which they suggest may be obtained from one to one therapy. Pascual-Leone et al. (49) suggested 14 individual sessions is appropriate for individuals with existing issues. It was on this basis that resilience was valued as 14 individual, psychotherapeutic sessions (see Table 3). The assumption that 14 individual psychotherapeutic sessions has a similar effect to a one-day workshop (e.g., the Create and Connect program) is admittedly contestable. However, a one-day workshop that focuses on creativity and connectedness can offer an intensive, immersive experience that might be considered similar to the impact of multiple counselling sessions (33, 50). Moreover, the unique therapeutic mechanisms of creative programs can lead to profound insights and emotional processing (51–53), potentially achieving in 1 day what might take multiple counselling sessions. The added dimension of group dynamics in these programs which emphasises peer support, can amplify the overall therapeutic impact (33, 50, 51), again potentially contributing to outcomes comparable to multiple individual counselling sessions.

The final outcome involves an increased sense of hope, optimism and possibility, which has been equated to future planning and projecting oneself into the future (54). In identifying a comparable proxy, we are suggesting that the programs offered by Satellite are comparable to having a mentor. Mentors help with goal setting and guidance with planning to achieve those goals; mentors also help young people navigate challenges, make important decisions, and offer advice on various aspects of life (55). Thus, in valuing this outcome, we are equating having a mentor to participating in Satellite programs, which likewise aim to build young people’s hope, optimism and a sense of possibility.

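### About 80% of the undiscounted per-participant value in Table 3 comes from the one outcome valued as an end state. The other two are valued at the price of a service, and the plan adds them without noting the mix

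*Protocol article*

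**What the plan says.** The section Giving outcomes a value states the criterion for the proxies: they are chosen "using financial proxies that reflect that importance of the outcome to stakeholders". Table 3 then sets three values for a six-month period.

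- **Belonging and connectedness.** The source study "identified the economic value of friends (in addition to existing friends): 15,500 pounds per year in 2007". This is uprated for inflation and "converted to 2022 AUD 42,818.76" a year, and the six-month value is entered as AUD 21,861.38.
- **Resilience.** The professional body "recommends $300 per hour per child/young person for psychological services". Fourteen sessions are assumed, giving "4,200 per child/young person" in dollars.
- **Hope, optimism and possibility.** The proxy is the "Cost of a mentor such as what might be available from" a named mentoring program, at a dollar price of "2,500 per person for 12 months", entered as AUD 1,250 for six months.

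The section Calculating the SROI sums these values, applies attribution, displacement, deadweight and drop-off, and divides by program cost. A ratio above one is read as benefits exceeding costs. Sensitivity is tested by moving each key assumption ±10% in turn, and by best, worse and moderate scenarios built from optimistic to pessimistic values.

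Table 2 (Mapping outcomes) records the youth council's votes: connectedness 9, belonging 8, reduced loneliness 7, reduced shame 7, help seeking 7, acceptance 7, understanding 6, improved coping 5. Giving outcomes a value reports that the council was consulted on likening connectedness and belonging to having friends. Limitations says that proxy choice can be subjective and that the currency conversion is imperfect. No section says that Table 3 combines two kinds of valuation.

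**The concern.** What an end state is worth to a person and what it costs to buy a service that might produce it are different quantities. The first can be many times the second for the same outcome. Adding one of the first kind to two of the second gives a total in which an outcome's weight depends partly on the basis it happened to receive.

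This matters because the outcome on the different basis is also by far the largest. The article expects the ratio to inform funding decisions and to be used in lobbying for funds, and it adopts the principles of transparency and of not overclaiming. A reader shown a ratio above one would need to know whether it would still be above one if all three outcomes were valued in the same way. The planned sensitivity analysis does not commit to answering that.

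**Working it through.** **Inputs (Table 3).** Connectedness C = 21,861.38; resilience R = 4,200; hope H = 1,250, all AUD per participant for six months. Stated annual value of connectedness = 42,818.76.

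**1. Reproducing the plan's figures.**
- R: 14 × 300 = 4,200. Agrees.
- H: 2,500 / 2 = 1,250. Agrees.
- C: 42,818.76 / 2 = 21,409.38, whereas Table 3 prints 21,861.38. The printed figure is 452.00 (2.1%) higher. This is a separate discrepancy to reconcile, and it barely affects what follows.

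**2. Share of the undiscounted sum.**
- As printed: C + R + H = 27,311.38. Shares are C 21,861.38 / 27,311.38 = 80.0%, R 15.4%, H 4.6%.
- With exact halving: 21,409.38 / 26,859.38 = 79.7%.

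**3. Share after deductions.** The numerator is defined after discounts, and these may differ by outcome. The section Deadweight and displacement uses the national cohort comparison for connectedness only (ages 14 and above) and interviews for the rest. The article gives no retention rates, so assume that 25% to 100% of value is kept, separately for C and for R + H = 5,450.
- Lowest: 0.25 × 21,861.38 = 5,465.35; 5,465.35 / (5,465.35 + 5,450) = 50%.
- Highest: 0.25 × 5,450 = 1,362.50; 21,861.38 / (21,861.38 + 1,362.50) = 94%.

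The share equals 80% only if all three outcomes have the same achievement and deductions.

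**4. Comparison with recorded importance.**
- Dollar ratio, connectedness to resilience: 21,861.38 / 4,200 = 5.2.
- Votes, connectedness to improved coping (the listed item nearest to resilience): 9 / 5 = 1.8.
- Votes, with connectedness, belonging and reduced loneliness pooled: (9 + 8 + 7) / 5 = 24 / 5 = 4.8.

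The order agrees either way. The size agrees only under pooling, and the article does not describe deriving any dollar value from votes, pooled or single.

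**5. Reach of the planned sensitivity step.** A ±10% change moves the undiscounted sum as follows:
- C: 2,186.14 / 27,311.38 = 8.0%
- R: 420 / 27,311.38 = 1.5%
- H: 125 / 27,311.38 = 0.5%

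**6. Illustration of a change of basis.** The article gives no service price for peer connection. Purely as an assumption, use its other two proxies as a range for C.
- C = 1,250: sum = 1,250 + 4,200 + 1,250 = 6,700, which is 25% of 27,311.38; connectedness share 1,250 / 6,700 = 19%.
- C = 4,200: sum = 4,200 + 4,200 + 1,250 = 9,650, which is 35% of 27,311.38; connectedness share 4,200 / 9,650 = 44%.

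The sum falls by about 65% to 75%, far outside what a ±10% step shows.

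**The case against.** The strongest reply has four parts.

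*Stakeholders did put connectedness first.* A reader might infer that the choice of basis, and not stakeholder importance, fixes the weights. The documents do not support that. The council ranked connectedness and belonging first and second, the article notes that several of its preferences overlap around this theme, the council was consulted on the friends analogy, and the pooled vote ratio is close to the dollar ratio. Nor does the absence of hope from Table 2 show that it was unimportant, because the Theory of Change, built later with the council and staff, includes it. What remains is that no dollar size is shown to come from stakeholder importance.

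*The illustration borrows its prices.* This is correct. Nothing in the article ties a mentoring or psychology fee to connectedness, so the 65% to 75% is not an estimate of overstatement. A common basis could also mean valuing resilience and hope as end states, which could raise the total.

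*The scenarios may cover it.* A sufficiently low pessimistic value for connectedness would have the same numerical effect, and a condensed article may leave such values to a fuller plan. But the scenarios are described as varying values, and nothing commits them to changing the basis or to telling the reader that it matters.

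*Subjectivity is disclosed, and the ratio is described as a social value currency rather than a financial value.* Both are true, but neither tells the reader that the largest component is measured on a different basis from the others.

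**Conclusion.** The point holds in a limited form. Table 3 mixes one end-state value with two service prices, the plan adds them, and no section notes or justifies this. The end-state outcome supplies 80.0% of the undiscounted per-participant sum (79.7% with exact halving). That figure rests only on Table 3.

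Three stronger readings are tempting but not supported. The 80% is not a share of the SROI numerator, which is taken after deductions; under the assumed retention rates it could lie anywhere from 50% to 94%. The basis does not explain the whole 80%, since connectedness would still hold 19% to 44% under the illustrative service prices. And nothing shows that the ratio would fall below one, because the article gives no program cost per participant.

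The defect is one of disclosure and of a missing sensitivity check. As planned, a reader could not tell whether a ratio above one depends on the valuation basis.

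**What to change.** 1. Keep the base case. State in Calculating the SROI and in Limitations that it combines an end-state value for connectedness with service prices for resilience and hope.
2. Add to the planned scenarios one pre-specified same-basis ratio, with connectedness valued at the cost of a service that provides peer connection and the source of that price given. Report it beside the base case and say whether the reading above one depends on the basis. It need not be a condition for claiming a positive return.
3. Qualify the sentence in Giving outcomes a value: importance to stakeholders guided the choice of outcomes and analogies, not the size of the dollar values.
4. While editing Table 3, reconcile 21,861.38 with half of 42,818.76.

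The cost is one further proxy search, one extra calculation and a few sentences. The downside for the authors is a second figure that will probably be less favourable.

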Create and Connect	8–17	These workshops are one-day programs that offer opportunities for participants to connect with peers in a safe, creative space. Various workshops are offered including music and song writing, photography and visual art such as graffiti and meme-making, plus other art and craft-based activities. Participants learn how to use music, photography, and art to express themselves, in an environment where they have the opportunity to connect with other young people who have a family member living with mental health challenges. The workshop allows participants to explore their personal and shared experiences through open dialogue and develop inclusive communication skills, including both visual and spoken language.
Satellite Connect in person or online	18–25	A structured peer support and peer development program that gives young people the space to be heard, learn new skills, and share their stories. Also covered is how their lived experience might be used to positively shape and influence the lives of younger children. Online versions of Satellite Connect run for 6 weeks, while in-person editions of Satellite Connect takes place across 3 weeks. During the program, participants meet other young people who have a family member living with mental health challenges, and interact, collaborate, and form connections with others living with similar families. Various themes are discussed including self-care and self-compassion, communicating creatively, talking about mental health, mental illness, language and stigma, and considering next steps for participants to practice newly acquired skills.

These programs were selected because they provide a good overview of participants’ ages and represent the capstone programs offered to young carers. Given they attract the most participants, this focus also provides rich data for analysis. The SROI covers the period of January 2023 through to June/July, 2024 with the final evaluation report to be delivered in August 2024.

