## Calculating the SROI

Calculating the SROI involves adding up the outcomes (value), applying the discounts (attribution, displacement, deadweight and drop off) and comparing the result to the investment or costs incurred in delivering the program. Costs involved for Satellite involve employing staff to facilitate programs (including administration and registration), insurance, venue hire, catering, materials and travel (Satellite sometimes pays for transport so that young people/children can attend programs). Expenses associated with reimbursing YAC members for their input and advice on the programs offered is also included. Our analysis spanned a six -month period only (as indicated in Table 3), which does not necessitate the use of a discount rate to account for the time value of money (58). As the timeframe is less than a year, no additional adjustments for the differing value of money over time were required.

Once the net present value of costs and outcomes have been established (taking into consideration drop off, deadweight and displacement), the final ratio can be calculated. The formula for calculating the return on investment is:

SROI ratio = Social value of stakeholder outcomes (discounted)

Cost of providing programs

According to Arvidson et al. (23), an SROI ratio greater than one indicates a positive return on investment, or in other words, where the benefits of the investment are greater than its costs. The calculation is based on proxy values, as outlined in Table 3.

As the results are influenced by non-quantitative variables and assumptions, a sensitivity analysis for the SROI will be calculated to promote robustness. After establishing a base case scenario as outlined above, each key assumption will be changed (by ±10%), one at a time, to ascertain how much the SROI ratio changes. Changes in the SROI will be compared for each variation and those assumptions that cause the most significant changes in the SROI ratio identified. Several plausible scenarios will be developed including best case, worse case and moderate scenarios, using most optimistic to most pessimistic values of each of the assumptions. Each of these scenarios will be reported including a discussion of which assumptions have the most significant impact on the SROI ratio.

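### The Table 3 proxies are not on a common price base, so the base-case SROI ratio is modestly biased, probably downward

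*Protocol article*

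**What the plan says.** Under Giving outcomes a value, the article explains that the friendship value was first calculated in 2007 and that "we adjusted it for inflation to reflect its current purchasing power". Table 3 gives the chain: "15,500 pounds per year in 2007 is equivalent to 23,903.38 pounds in 2022, converted to 2022 AUD 42,818.76" per annum, with a six-month value of AUD 21,861.38.

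The resilience row rests on a psychological society's website, which "recommends $300 per hour per child/young person for psychological services – 14 sessions", giving AUD 4,200. No date or price year is attached.

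The hope row uses a mentoring cost of AUD "2,500 per person for 12 months", entered as AUD 1,250 for six months. Its source is the "Big Brother, Big Sisters of Australia Annual Report 2019–2020", and no uprating is described.

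Under Establishing scope and identifying stakeholders: "The SROI covers the period of January 2023 through to June/July, 2024". Calculating the SROI lists the cost items ("Costs involved for Satellite involve employing staff to facilitate programs (including administration and registration), insurance, venue hire, catering, materials and travel", plus advisory council reimbursement) without a price year. It bases the ratio on the Table 3 values and says that, because the horizon is under a year, neither a discount rate nor any further time-value adjustment is needed.

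**The concern.** A benefit-cost ratio needs numerator and denominator at one price level. The authors accept this for the friendship value, since they uprate it from 2007. But the uprating ends the year before the program period begins, the same step is not applied to the mentor value, and the fee cannot be placed in time. No base year is stated for proxies or costs.

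The six-month argument in Calculating the SROI settles discounting within the horizon. It does not address proxies drawn from different years, yet a reader could take it as a reason to leave them alone.

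These are final dollar figures that feed the headline ratio directly, and the article expects that ratio to be used in seeking funding from government and philanthropists.

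**Working it through.** **Reproducing Table 3**

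- Resilience: 14 × 300 = 4,200, as stated.
- Hope: 2,500 / 2 = 1,250, as stated.
- Friendship: 42,818.76 / 2 = 21,409.38, against 21,861.38 stated. The difference is 452.00, or 452.00 / 21,409.38 = 2.1%. The stated half-year value implies 2 × 21,861.38 = 43,722.76 a year. Either the annual or the six-month figure is wrong.

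**Weights.** The stated sum is 21,861.38 + 4,200 + 1,250 = 27,311.38. The shares are friendship 80.0%, resilience 15.4% and hope 4.6%.

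**Time lags.** The midpoint of January 2023 to June/July 2024 is about October 2023. From mid-2022 that is about 1.25 years, so 1 to 1.5 years is used for friendship. From the middle of 2019-20 (read as a financial year) it is about 3.75 years, so 3.5 to 4 years is used for the mentor value. The undated fee is left unchanged.

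**Uprated sum** = 21,861.38 × (1+g)^t1 + 4,200 + 1,250 × (1+g)^t2, where g is annual price growth. The documents give no Australian index, so g is an assumption.

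| g | t1 = 1, t2 = 3.5 | t1 = 1.5, t2 = 4 |
|---|---|---|
| 2% | 27,838 (+1.9%) | 28,074 (+2.8%) |
| 4% | 28,370 (+3.9%) | 28,848 (+5.6%) |
| 6% | 28,906 (+5.8%) | 29,636 (+8.5%) |
| 8% | 29,447 (+7.8%) | 30,437 (+11.4%) |

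The only inflation rate implied by the article is the UK one in the friendship row: (23,903.38 / 15,500)^(1/15) − 1 = 2.93% a year. Used as g, it gives +2.8% to +4.1%.

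**Where the shift comes from.** Uprating the mentor value alone moves the sum by 0.3% (g = 2%, 3.5 years) to 1.2% (g = 6%, 4 years). The friendship row supplies the rest: 1.6% to 7.3%.

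**If the fee also lagged by one year**, the figures for 1.5 and 4 years become +3.1% at 2% and +9.4% at 6%.

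**Interaction with the halving discrepancy.** If 42,818.76 is right, the starting sum is 21,409.38 + 4,200 + 1,250 = 26,859.38.

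- At g = 2% with lags of 1 and 4 years, the uprated sum is 21,837.57 + 4,200 + 1,353.04 = 27,390.61, which is +0.3% against the stated 27,311.38.
- At g = 8% with lags of 1.5 and 4 years, it is 29,929.83, or +9.6%.

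**From sum to ratio.** The ratio moves by the same percentage as the sum only if all three outcomes are credited equally and the later deductions are the same percentages in each row. Otherwise the shift depends on how much of each row survives those deductions.

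**The case against.** The strongest reply is that this is small, conservative and already covered. If prices rose, older proxies understate benefit, which fits the adopted principle of not overclaiming. 2022 is the last full year before the period starts, this is a forecast SROI, and the article claims only an approximation. It also plans one-at-a-time variation of ±10% with best-case and worst-case scenarios, and its limitations concede that the updated friendship value may miss economic changes.

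Much of this stands on size and direction. At 2% to 6% growth, the friendship row's own shift (2.0% to 9.1%) lies inside ±10%. It does not remove the point. A lag that moves two rows together in one probable direction is a correctable base-case error, not an uncertainty to be varied symmetrically one row at a time. The limitation covers only the friendship value. The mentor row's own shift (7.2% at g = 2% over 3.5 years to 26.2% at g = 6% over 4 years) mostly exceeds ±10%, although the row carries little weight.

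A reader might infer more than the article supports:

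- *That the proxies sit in three known, different price years.* The fee is undated; it may or may not match the program period.
- *That costs are stated in 2023-24 prices.* No cost year is given; it is inferred from the period covered.
- *That the protocol forbids price-level correction.* The sentence on further adjustment is tied to the six-month horizon and is best read as being about discounting.
- *That the dollars cannot be compared at all.* A shift of a few per cent does not support that.

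**Conclusion.** The point holds in a limited form. Two proxies have source years before the program period, one is undated, and no base year is stated, so the numerator is not on one price base and the description of the friendship value as current is not met by a figure labelled "converted to 2022 AUD 42,818.76". For assumed inflation of 2% to 6% a year, the stated proxy sum is about 2% to 9% too low before deductions, and the base-case ratio is probably too low by a similar proportion. This rests on rising prices, costs in program-period prices, and the fee being roughly current. If the stated annual friendship value is correct, the 2.1% halving overstatement partly offsets the lag, and the net change from the stated sum is about +0.3% to +9.6% for 2% to 8% inflation. The ratio is biased, not invalidated.

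**What to change.** 1. Reconcile the friendship row first: correct either the annual or the six-month figure so that one is half of the other.
2. State one price year for the analysis, matching the year or years in which program costs were incurred, and state the price year of the costs.
3. Record the date and price year of the psychologist fee.
4. Uprate every proxy dated before the chosen year with one named Australian index. Add the source year, index factor and final value to each row of Table 3, and use the final values in the base case.
5. In Calculating the SROI, limit the statement about needing no further adjustment to discounting over the six-month horizon.

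The cost is two or three multiplications, extra columns in Table 3 and a reworded sentence. No new participant data are needed.

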## Limitations

A potential limitation inherent in any SROI study is the monetisation of outcomes (28) and a lack of a universal bank of indicators (59). However, even those things with a market value are valued subjectively based on market conditions and consumer preferences. It was challenging to identify financial proxies for the various outcomes in this study, especially in relation to resilience as it comprised of multiple factors. As pointed out by Mook et al. (60), the choice of financial proxies can become subjective, which can compromise the reliability of the SROI. Given these challenges, Nicholls et al. (26) highlighted the importance of being transparent about the development and identification of these proxies which this protocol aims to do. Nonetheless, we agree with the notion purported by Arvidson et al. [(23), p. 233] when they argued that excluding significant outcomes which may be challenging to place a monetary value on, would “render the analysis precisely wrong, rather than the desirable “roughly right” and would greatly diminish the perceived social value of a given program.

We acknowledge the relatively short-term nature of the study and our subsequent inability to track long term change (or lack thereof). The study would have been strengthened had we been able to locate a comparison group for children under 14 years of age and for other outcomes besides connectedness. Using a currency converter to update the 2007 value of friendships presents a limitation in our analysis and may not fully capture more nuanced economic changes over time. We also acknowledge that the decision to aggregate the number of programs without employing a weighting system may limit the analysis. Similarly, the various programs offered by Satellite are delivered by different facilitators. As the knowledge, experience, skill and interpersonal style of group facilitators can have a significant impact on program outcomes (61), it will be difficult to determine which specific program/s are responsible for participant outcomes. Nonetheless, we are collecting fidelity logbooks to document the consistency of program delivery (30).

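### The friendship proxy, about 80% of the per-person proxy sum, is carried from pounds to Australian dollars with a currency converter, a step that does not preserve purchasing power between the two countries

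*Protocol article*

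**What the plan says.** In the section on giving outcomes a value, belonging and connectedness are valued as having additional friends, using a published UK estimate. Table 3 gives the chain: "15,500 pounds per year in 2007 is equivalent to 23,903.38 pounds in 2022, converted to 2022 AUD 42,818.76" per annum. The six-month value printed in the same row is $21,861.38. The text says that the inflation adjustment is there to bring the 2007 figure to present purchasing power, and then adds: "Although using a currency converter may not be the ideal method, this approach, when combined with inflation adjustments, provides a reasonable approximation" of the value today.

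The Limitations section returns to the point: "Using a currency converter to update the 2007 value of friendships presents a limitation in our analysis". The reason given there is that finer economic changes over time may be missed.

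The other two proxies in Table 3 start in Australian dollars: "4,200 per child/young person" for resilience, and half of "2,500 per person for 12 months" for hope. Friendship is the only proxy that crosses a border.

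The section on calculating the SROI bases the ratio on the Table 3 values. It plans to vary each key assumption by 10% either way, one at a time, and to report best, worse and moderate scenarios. It does not list which assumptions count as key.

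**The concern.** Two separate adjustments are needed to use a 2007 UK value in Australia. One moves it through time and the other moves it between countries. The plan does the first with UK inflation and the second with a currency converter, which is apparently a market rate. A market rate need not match the relative cost of living in the two countries. Friendship is not traded, so what should be carried across is what the sum would buy. Inflating in pounds beforehand cannot correct this, because that step never leaves the UK. The defence in the text, that the converter is acceptable when combined with inflation adjustment, therefore does not meet the weakness.

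The step falls on the largest of the three proxies. Any gap between parity and the rate used is carried into the base-case social value, and the Conclusion says that the findings may be used to lobby government and philanthropic funders.

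**Working it through.** **Inputs (all from Table 3).** Friendship: £15,500 a year in 2007, £23,903.38 in 2022, AUD 42,818.76 a year, printed six-month value AUD 21,861.38. Resilience: 14 × 300 = AUD 4,200. Hope: 2,500 / 2 = AUD 1,250.

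**1. The plan's own chain.**
- Inflation factor: 23,903.38 / 15,500 = 1.5422, or 1.5422^(1/15) − 1 = 2.93% a year over 15 years. No index is named.
- Conversion rate: 42,818.76 / 23,903.38 = 1.7913 AUD per GBP. No source or date beyond the year 2022 is given.
- Six-month value: 42,818.76 / 2 = 21,409.38. The printed 21,861.38 does not reproduce. It is 452.00 (2.1%) higher and would need an annual value of 43,722.76, a rate of 43,722.76 / 23,903.38 = 1.8291.

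**2. Share of the per-person proxy sum** (equal counts per outcome, before deadweight, attribution, displacement and drop-off).
- From the halved annual figure: 21,409.38 / (21,409.38 + 4,200 + 1,250) = 21,409.38 / 26,859.38 = 79.7%.
- From the printed figure: 21,861.38 / 27,311.38 = 80.0%.

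**3. Sensitivity of the sum to the conversion factor.** A 10% gap moves the proxy by 0.10 × 21,409.38 = 2,140.94, and the sum by 2,140.94 / 26,859.38 = 8.0%.

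The documents contain no parity factor, so the factors below are assumptions chosen to show a range. Six-month value = 23,903.38 × r / 2; sum = that value + 5,450.

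| Assumed r (AUD per GBP) | Six-month friendship value | Three-proxy sum | Change from 26,859.38 |
|---|---|---|---|
| 1.6 | 19,122.70 | 24,572.70 | −8.5% |
| 1.7 | 20,317.87 | 25,767.87 | −4.1% |
| 1.7913 (implied by plan) | 21,409 | 26,859 | 0 |
| 1.9 | 22,708.21 | 28,158.21 | +4.8% |
| 2.0 | 23,903.38 | 29,353.38 | +9.3% |
| 2.2 | 26,293.72 | 31,743.72 | +18.2% |

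Expressed as gaps from the implied rate, 20% either way takes the sum to 22,577.50 or 31,141.26, a change of 15.9%.

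**The case against.** The strongest reply is that the choice is disclosed twice and defended, so the plan hides nothing and contradicts nothing. That is right. The text says only that the converter may fall short of ideal; a reader might infer that the authors concede the method is wrong, and they do not. Disclosure answers only part of the point, however: the defence in the text rests on inflation and the stated limitation concerns change over time, while the cross-country step is not discussed.

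A second reply is that no effect has been shown. This also stands. A gap near zero is as compatible with the documents as one of 20%, and the table above shows leverage, not bias. A reader might infer that the ratio is inflated; nothing in the documents gives a direction. That the converter used a market rate is likewise an inference, since no rate type is stated.

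A third reply is that the planned sensitivity analysis covers it. If the friendship proxy is one of the key assumptions, moving it by 10% is the same as moving the conversion factor by 10%. But the conversion is not named as an assumption, 10% may not span the gap, and varying around a base case leaves that base case as it is.

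Two further readings go too far. One is that a gap would pass almost whole into the ratio. The 80% is a share of per-person values; the share of the final numerator depends on how many participants change on each outcome and on the deductions, which may differ by outcome because only connectedness has the LSAC comparison. The other is that the ratio would float with the exchange rate. Table 3 fixes the conversion at 2022, and a parity factor needs a chosen year too.

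**Conclusion.** The point holds as a cheap improvement to a stated method. For a non-traded value, a purchasing-power conversion fits the aim of reflecting purchasing power better than a currency converter does, and UK inflation does not substitute for it. On equal counts per outcome and before deductions, each 10% gap between parity and the implied rate of 1.7913 moves the three-proxy sum by about 8.0%. The size and direction of the actual gap, and its effect on the final ratio, cannot be determined from the documents.

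The mismatch between the printed $21,861.38 and $21,409.38 is a separate matter. It is demonstrable from Table 3 alone and leaves unclear which conversion rate lies behind the figure that enters the ratio (1.7913 or 1.8291).

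**What to change.** In Table 3, convert the 2022 pound value with a named, published UK-Australia purchasing-power-parity factor for a stated year, and name the inflation index. Keep the currency-converter figure as a named sensitivity scenario, with its rate, source and date. In the section on calculating the SROI, list the conversion factor among the assumptions to be varied, with a range wide enough to include both the parity and the converter value. In the same edit, reconcile the printed six-month value with half of the annual figure.

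This takes one recalculation and a few lines of text, with no new participant data. The downside is that the headline friendship proxy changes, in a direction not known in advance.
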